### Study hypotheses and principal comparisons

The main hypothesis is that multi-dose activated charcoal will reduce the case fatality rate from 10% to 7%, hence the first principal comparison will be multi-dose activated charcoal versus no intervention. The potential of multidose regimens to work long after ingestion – due to interruption of enterohepatic circulation and gut dialysis – means that such a regimen is more likely to work in a situation where people typically present several hours after ingestion.

We suspected that a single dose of charcoal would be less effective since most poison absorption will have taken place by the time the patients present to hospital. Therefore, the second principal comparison will test the hypothesis that the case fatality rate in patients receiving a single dose of activated charcoal is equal to that in patients receiving multiple doses.

In order to investigate whether a single dose of activated charcoal has a similar effect as giving no intervention, the third principal comparison will test the hypothesis that the case fatality rate in patients receiving a single dose of activated charcoal is equal to that in patients receiving no intervention.

### Statistical analysis

The main analysis will be carried out on an intention-to-treat basis, using the chi -squared test for the primary outcome (or Fisher's exact test if appropriate) and for other dichotomous outcomes. Odds ratios (plus 95% confidence intervals) will be reported to establish magnitude and direction of the treatment effect. In the original protocol, we indicated that risk would be the chosen measure of effect; however, in order to be able to adjust the treatment effect estimate for stratification variables in future analyses, we will calculate odds instead, using logistic regression. Since the primary outcome is an uncommon event, risk and odds should be similar.

For outcomes where time-to-event is recorded, we will use the logrank test to compare treatment groups, produce Kaplan-Meier curves to illustrate the comparison, calculate incidence rates and perform Cox's regression to estimate hazard ratios, adjusted for stratification factors.

An analysis of trends in treatment effect for factors 'reported time from ingestion to treatment' and 'patient status on admission' will be performed.

It is possible that both treatment regimens, if effective in reducing case fatality rates, will be more effective the earlier they are started. Therefore we will assess the trends in clinical effectiveness according to time post-ingestion to start of therapy using statistical modelling techniques. In order to determine whether treatment should be started irrespective of severity, we will likewise also assess trends in case fatality rates across a gradient of severity.

Admission blood samples will be retrospectively analysed to determine the identity of the poison ingested. The primary analyses will be repeated using the confirmed identity of the poison.

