### Randomisation

Patients were randomised into one of three study arms. The random allocation sequence was generated by computer and incorporated into a Microsoft Access programme written for patient recruitment, randomisation and event recording (Figure 1). Stratified block randomisation was performed using the following strata: (i) the toxin stated to have been ingested (oleander, organophosphate or carbamate, organochlorine, other pesticide or unknown pesticide or paraquat, medicine or unknown) ; (ii) reported time between poisoning and recruitment (<1 hr; 1–4 hrs; >4 hrs; unknown); and (iii) status on admission (Asymptomatic, Symptomatic with GCS 14 or 15/15, Symptomatic with GCS <14).

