**Figure 1 F1:**
[figure not shown]
The hand held computer used to recruit and randomise patients and to record all events. Randomisation was performed at the patient's bedside. Allocation could not be predicted by the study doctor.

The allocation sequences were generated independently by the study statistician (EJ) and implemented by the programmer (SA), neither of whom had a role in patient recruitment, treatment or assessment. Variable block sizes of 3, 6 and 9 were used to allocate patients in equal numbers to each treatment group i.e. ratio 1:1:1 using Stata v7 software (ralloc subroutine version 3.2.5).

Participants were recruited and randomised by a study doctor at the bedside using a dedicated handheld computer at each study hospital (Figure 1). Randomisation occurred after the patient's baseline data had been entered and receipt of consent noted, and could not be manipulated by study doctors. The recruiting doctor was unable to predict allocation before randomisation.

All practical steps were taken to avoid bias: (i) the randomisation program was designed to be rapid and simple to operate, and yet remain independent of the investigators; (ii) the next treatment allocation could not be predicted in advance; (iii) the primary outcome, vital status at discharge, was unambiguous, and the secondary outcomes were objective; (iv) all outcomes were recorded systematically by the study team, not other hospital physicians; (v) patient follow-up was expected to be near 100% complete; and (vi) the analysis will be performed on an intention-to-treat basis.

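### The main test of in-hospital death ignores the factors used to stratify randomisation; it is valid and adequately powered, but conservative to the extent that those factors predict death

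*Protocol article*

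**What the plan says.** The Randomisation section of the protocol article says: "Stratified block randomisation was performed using the following strata". It then lists reported toxin, reported time between poisoning and recruitment, and status on admission. Blocks were permuted: "Variable block sizes of 3, 6 and 9 were used to allocate patients in equal numbers to each treatment group i.e. ratio 1:1:1".

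The Statistical analysis section names the main test of death: "The main analysis will be carried out on an intention-to-treat basis, using the chi -squared test for the primary outcome", with Fisher's exact test as the alternative where appropriate. Neither test uses the strata. On the effect measure, the authors moved from risks to odds: "in order to be able to adjust the treatment effect estimate for stratification variables in future analyses, we will calculate odds instead, using logistic regression". For outcomes with recorded times, an unstratified logrank test comes first, after which they will "perform Cox's regression to estimate hazard ratios, adjusted for stratification factors".

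The Sample size section plans 1400 patients per arm to detect 10% against 7% mortality, with alpha 5% and power 80%.

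**The concern.** Permuted blocks within strata make the arms nearly equal in their mix of toxin, delay and admission status. The difference in deaths between arms then varies less from one randomisation to another than under simple randomisation. A pooled chi-squared test does not know this. Its standard error still includes the between-stratum variation in risk that the design has removed. If the strata predict death, the standard error is too large, the true type I error falls below 5%, and power is lost that the same data could have given.

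There is some indication in the article that the strata matter. The Background puts case fatality in Sri Lanka at around 10% overall and above 50% for some pesticides. The plan also includes trends and subgroups by all three factors.

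A missed benefit would be costly: the Discussion says that a finding of no effect could lead to money now spent on charcoal being moved elsewhere. In addition, adjusted and unadjusted odds ratios answer slightly different questions, so it should be fixed before results are seen which of them is primary.

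**Working it through.** **1. The plan's own figure.** Inputs from the Sample size section are 10% and 7%, alpha 5% (two-sided assumed, as it is not stated), power 80% and no loss to follow-up. With mean risk 0.085:

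n = [1.96 × √(2 × 0.085 × 0.915) + 0.8416 × √(0.10 × 0.90 + 0.07 × 0.93)]² / 0.03² = [0.7730 + 0.3315]² / 0.0009 ≈ 1356 per arm.

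With continuity correction this becomes 1422. At the planned 1400, power is 81.3%. The stated size is thus reproduced, and it rests on an unadjusted comparison of two proportions.

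**2. Effect of ignoring the strata.** Let R² be the between-stratum variance of risk divided by p(1 − p), and k = √(1 − R²). With good balance within strata, the true standard error of the risk difference is about k times the one used by the pooled test. Hence:

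- true type I error of the unadjusted test = 2[1 − Φ(1.96/k)]
- power, unadjusted = Φ[(0.03 − 1.96·se₀)/(k·se₁)]
- power, stratified = Φ[(0.03 − 1.96·k·se₀)/(k·se₁)]

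Here se₀ = √(0.15555/1400) = 0.01054 and se₁ = √(0.1551/1400) = 0.01053.

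For R² = 0.15, k = 0.922 and 1.96/0.922 = 2.126, which gives a type I error of 3.4%. Power is Φ(0.96) = 83.2% unadjusted and Φ(1.13) = 87.1% stratified.

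| Assumed R² | k | Type I error, unadjusted | Power, unadjusted | Power, stratified |
|---|---|---|---|---|
| 0.05 | 0.975 | 4.4% | 81.9% | 83.2% |
| 0.10 | 0.949 | 3.9% | 82.5% | 85.1% |
| 0.15 | 0.922 | 3.4% | 83.2% | 87.1% |
| 0.20 | 0.894 | 2.8% | 83.9% | 89.0% |
| 0.30 | 0.837 | 1.9% | 85.6% | 92.6% |

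**3. Check by simulation.** Reading the toxin list as five levels, there are 5 × 4 × 3 = 60 cells. Trials of 4200 patients were simulated with blocks of 3, 6 and 9, overall risks of 10% and 7%, and a constant odds ratio across cells (6000 runs per setting). The chi-squared test was compared with a Mantel-Haenszel test over the cells.

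| R² | Control risk across cells | Type I error: unadjusted / stratified | Power: unadjusted / stratified |
|---|---|---|---|
| 0.035 | 2.4% to 29.4% | 4.5% / 4.7% | 82.4% / 83.1% |
| 0.144 | 0.4% to 55.1% | 3.7% / 5.2% | 82.1% / 86.1% |
| 0.295 | 0.1% to 75.7% | 2.0% / 4.8% | 84.4% / 91.1% |

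The power difference is 0.7, 4.0 and 6.7 points. With separate sequences in three hospitals (180 cells, R² 0.144, 4000 runs), type I error was 3.7% against 5.4% and power 82.3% against 85.3%.

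**4. What R² could be.** As an illustration only, take control risks of 2%, 8% and 39% in 45%, 40% and 15% of patients by admission status. The mean is 0.0995 and the between-stratum variance is 0.0157, so R² = 0.0157/0.0896 ≈ 0.17. None of these risks or shares is in the article.

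**5. Scale of the estimate.** The unadjusted log odds ratio for 10% against 7% is ln[(0.07/0.93)/(0.10/0.90)] = −0.39. In the three simulated settings the conditional log odds ratio was −0.40, −0.45 and −0.54. An adjusted logistic model gains power because its estimate lies further from 1, not because its log-odds interval is narrower.

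**The case against.** The strongest reply is that nothing is broken. The chi-squared test keeps its type I error at or below 5%, it matches the sample-size calculation, and its power is above 80% in every setting examined. More than 4500 patients were recruited (Background). At about 1500 per arm the same formula gives about 84% even before any gain from stratification. This stands: a reader might infer that the trial is underpowered or its main test invalid, and the article supports neither.

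Second, the size is assumed. The figure above 50% concerns individual pesticides, while the randomisation levels pool paraquat with other and unknown pesticides, and organophosphates with carbamates, which may dilute that contrast. Nothing shows how strongly delay or admission status predicts death. This also stands. To call the strata strong predictors goes beyond the article, and with weak strata the loss is under one point.

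Third, a reader might infer that the reported odds-ratio intervals would shrink by the factor k. That factor belongs to the risk difference; it does not carry over to an adjusted log odds ratio.

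Fourth, the adjusted Cox models might be read as a contradiction. They are not: the logrank test is also stated without stratification, so both sets of comparisons start unadjusted. The difference is that the adjusted hazard ratio is part of the stated analysis, whereas the adjusted odds ratio is deferred.

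Fifth, the article says recruitment was done "using a dedicated handheld computer at each study hospital". That may suggest one sequence per hospital, but separate sequences are not stated and hospital is not a listed stratum.

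What survives is the mismatch between design and main test. The article names this test itself, so the choice has not simply been left to a separate analysis plan.

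**Conclusion.** The point holds as one of efficiency. The main test of death leaves out the factors by which patients were randomised and is therefore conservative to the extent that they predict death. Over an assumed R² of about 0.04 to 0.30, the true type I error is about 4.5% down to 2%, and about 1 to 7 points of power are given up against a stratified test (about 4 points near R² 0.15). These figures assume 1400 per arm, 10% against 7%, two-sided 5%, near-complete balance within cells and a constant odds ratio. The direction follows from the design; the size cannot be settled from the article. The improvement is cheap and worth making, but the plan is usable without it.

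**What to change.** - Make the primary comparison of in-hospital death either a Mantel-Haenszel test stratified by the three randomisation factors, with a stated rule for pooling sparse cells, or a logistic regression on treatment with the three factors as main effects. With 60 cells, 4200 patients average only 70 per cell over all arms, so a model with every cell as its own term is unwise.
- Keep the unadjusted chi-squared test and odds ratio as supporting analyses.
- State that the adjusted odds ratio is conditional on the factors and will tend to lie further from 1 than the unadjusted one, so that the two are not read as conflicting. State also that the gain is in power and not in a narrower log-odds interval.
- Hospital may be added as a covariate. Say whether each hospital had its own sequence.

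Cost: no new data are needed, since baseline data were entered before randomisation. There is a small cost in credibility. The Background says that the final analysis is under way, and the trial statistician supplied the interim analyses to the monitoring committee. The change must therefore be dated and made without reference to results by arm. If that cannot be shown, leave the chi-squared test as primary and report the adjusted analysis beside it with equal prominence.

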## Background

Deliberate self-poisoning is a major clinical problem in many parts of the developing world where highly toxic poisons and sparse medical facilities ensure a high fatality rate [1,2]. Pesticides are the major problem – the WHO estimates that they cause more than 220,000 deaths globally each year, of which most are due to organophosphorus (OP) insecticides [3]. But other poisons, in particular plants, other pesticides, and some pharmaceuticals are locally important problems [1].

Self-poisoning is particularly important in Sri Lanka where thousands of people die each year and preventing suicide has become a national public health priority [4,5]. The case fatality for self-poisoning in Sri Lanka is around 10%[1] but increases to over 50% for some pesticides [6]. More effective medical management is urgently required [7,8].

Current management of self-poisoning involves resuscitation and stabilisation of the patient, administration of antidotes where available, and gastric decontamination [9]. Mechanical forced emesis and gastric lavage are routinely used in Sri Lanka and other parts of Asia, despite little evidence for benefit [10,11]. Activated charcoal is available in some hospitals but is not routinely used in all, due to doubts about its effectiveness.

Animal and simulated human overdose studies have shown that a single dose of activated charcoal, if given soon after a poison is ingested, can reduce absorption of the poison [12]. The ability of charcoal to prevent absorption of poison falls off rapidly within one hour. Multi-dose regimens of charcoal may be effective much later for some poisons since the presence of activated charcoal in the intestine will interrupt the enterohepatic circulation [13,14] and may also draw poison out of the gut vasculature into the bowel [15].

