### Sample size

In both hospitals, at least 10% of poisoned patients die before discharge [1]. An absolute reduction of 3% will be clinically important. In order to be able to detect whether either regimen of activated charcoal reduced the death rate from 10% to 7%, with a significance level (alpha) of 5% and a power of 80%, a minimum of 1400 patients had to be recruited to each arm of the trial (i.e. 4,200 patients in total).

Sample size calculations were based on current practice and a case fatality rate of 10%. The Independent Data Monitoring and Ethics Committee (IDMEC) was asked to review the recruitment and event rates during the first year of the trial in order to make recommendations about expanding the trial by including further hospitals if necessary.

There should have been no loss to follow up for the primary outcome. Patients were either discharged alive from the wards or their bodies transferred to the morgue for judicial autopsy. All secondary outcomes were assessed in hospital before discharge.

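### The reassurance that odds and risk are similar holds for the overall unadjusted mortality result, but need not hold for the stratification-adjusted odds ratio or high-mortality subgroups, and adjustment does not require odds

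*Protocol article*

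**What the plan says.** The Statistical analysis section sets an intention-to-treat chi-squared test (or Fisher's exact test) for in-hospital death and reports odds ratios with 95% confidence intervals. It discloses a change of effect measure: "In the original protocol, we indicated that risk would be the chosen measure of effect". The reason given is that logistic regression on the odds scale will allow adjustment for the stratification variables in future analyses. The reader is then told: "Since the primary outcome is an uncommon event, risk and odds should be similar".

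Three other places bear on this:

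- **Sample size** and **Study hypotheses and principal comparisons** put the question on the risk scale, as a fall in case fatality from 10% to 7%: "An absolute reduction of 3% will be clinically important".
- **Background** puts case fatality for self-poisoning in Sri Lanka at around 10% overall, but says that it "increases to over 50% for some pesticides".
- **Randomisation** stratifies by poison, reported time since ingestion and status on admission (from asymptomatic to symptomatic with GCS below 14). **Pre-specified subgroup analysis** plans interaction or trend tests on mortality by poison, time and severity.

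**The concern.** Two steps in the argument do not carry as far as they are taken.

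First, adjustment is given as the reason for leaving the risk scale, but it does not force that move. Adjusted risk differences and risk ratios can be had from the same logistic model by standardisation, from Mantel-Haenszel methods, or from a log-link model.

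Second, the rare-event argument applies to the overall unadjusted comparison, whereas odds were chosen for the sake of the adjusted one. The odds ratio is non-collapsible: conditioning on prognostic strata moves it away from 1 even when randomisation has removed all confounding. With mortality ranging from about 10% overall to more than half for some pesticides, the strata may well be strongly prognostic. The approximation also weakens in any subgroup where death is common.

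At stake is how the result is read. Someone who relies on the reassurance could take an adjusted odds ratio for a risk ratio and credit charcoal with a larger mortality reduction than it produced. The effect estimate would also not be directly on the absolute scale that the trial uses to define clinical importance.

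**Working it through.** **Inputs from the article.** Control mortality 10%, charcoal mortality 7%, alpha 5%, power 80%, 1400 per arm (Sample size); about 10% overall and over 50% for some pesticides (Background). **Assumed:** a two-sided test, and the mortality and share of patients in each stratum, none of which the article gives.

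**1. The plan's own figure.** n = [1.96·√(2·0.085·0.915) + 0.8416·√(0.09 + 0.0651)]² / 0.03² = 1356 per arm, or 1422 with continuity correction. Power at 1400 per arm is 81.3%. The stated 1400 is reproduced. It rests on a comparison of two proportions, so the choice of effect measure does not touch it.

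**2. Overall unadjusted estimate.** RR = 0.07/0.10 = 0.70. OR = (0.07/0.93)/(0.10/0.90) = 0.0753/0.1111 = 0.677. With 98 v 140 deaths in 1400 per arm:

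- SE(log RR) = √(1/98 − 1/1400 + 1/140 − 1/1400) = 0.126; 95% CI 0.55 to 0.90.
- SE(log OR) = √(1/98 + 1/1302 + 1/140 + 1/1260) = 0.138; 95% CI 0.52 to 0.89.

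The gap of 0.023 is small beside either interval.

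**3. Subgroups.** For a constant RR of 0.70 at baseline risk p, OR = [0.7p/(1 − 0.7p)]/[p/(1 − p)].

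| Baseline mortality | OR equivalent to RR 0.70 |
|---|---|
| 5% | 0.689 |
| 10% | 0.677 |
| 30% | 0.620 |
| 50% | 0.538 |
| 60% | 0.483 |

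Conversely, a constant OR of 0.677 at 50% baseline gives a treated risk of 0.677/1.677 = 40.4%, which is RR 0.81, against 0.70 at 10% baseline.

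**4. Stratification-adjusted odds ratio.** For strata with shares w and control risks p averaging 10%, find the common within-stratum OR that makes the average treated risk 7%: Σ w·[OR·p/(1 − p)]/[1 + OR·p/(1 − p)] = 0.07.

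| Assumed stratum mortality (shares) | Adjusted OR | Reduction if read as a risk ratio |
|---|---|---|
| 5%/15% (50/50) | 0.671 | 33% |
| 3%/10%/38% (60/25/15) | 0.634 | 37% |
| 5%/50% (88.9/11.1) | 0.613 | 39% |
| 2%/60% (86.2/13.8) | 0.526 | 47% |

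The true risk reduction is 30% in every row.

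**5. The adjusted risk measures are available.** Standardise the 5%/50% row. With OR 0.613 the treated risks are 3.1% and 38.0%, so the average is 0.889·0.0313 + 0.111·0.380 = 0.0278 + 0.0422 = 7.0%. The same logistic model therefore returns a risk difference of 3 points and RR 0.70. Separately, a log-link Poisson model adjusted for the same strata returned RR 0.70 in every row when the true risk ratio was held constant at 0.70.

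**The case against.** The strongest reply is that the sentence is correct for what it most naturally describes, overall in-hospital death at about 10%. That stands: 0.677 and 0.70 are similar, and the sentence should be limited rather than called wrong.

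A reader might infer that the plan will overstate the benefit of charcoal. The document does not support this. The adjusted odds ratio is a valid estimate of a different quantity; it misleads only if there is an effect and it is read as a risk ratio. With no effect, both measures equal 1. The main test is the unadjusted chi-squared test, and adjustment is tied to future analyses, so significance and sample size do not change.

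The adjusted figures also depend on stratum risks and shares that had to be assumed, and with weakly prognostic strata the shift is trivial (0.671 against 0.677). The Background's high fatality concerns some pesticides, while the planned poison subgroups are broad; nothing shows that any analysed subgroup reaches 50%. Scale dependence of interaction runs both ways: a constant risk ratio gives varying odds ratios, and the reverse. It is no proof that the odds scale is the wrong one.

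Finally, logistic regression with odds ratios is conventional, the change is openly disclosed, and nothing rules out also reporting deaths and percentages by arm. Making the odds ratio secondary would be a matter of preference.

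Two things remain after all this. The stated reason for leaving risk does not require it, and the reassurance is worded without the limit that it needs.

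**Conclusion.** The point holds as a matter of reporting and interpretation. Similarity is right for the overall unadjusted estimate (RR 0.70, OR 0.677). It need not extend to the stratification-adjusted odds ratio or to high-mortality poison or severity subgroups, where at 50% baseline a risk ratio of 0.70 is an odds ratio of 0.54.

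If charcoal works and the adjusted odds ratio is read as a risk ratio, a true 30% reduction would look like one of 33% to 47% across the assumed strata. Where in that range the trial would fall cannot be told from the article, because it depends on stratum mortality and stratum shares that are not given. The 50% example likewise assumes a subgroup with that baseline risk.

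It would go too far to conclude that the similarity claim is simply false, or that the primary test or the sample size is compromised. Neither follows from the document.

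**What to change.** In the Statistical analysis section:

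- Report the risk difference and the risk ratio with 95% confidence intervals beside the odds ratio, both crude and stratification-adjusted. Obtain the adjusted versions by standardising the logistic model already planned: predict each patient's risk under each arm, average, then take the difference and the ratio. This puts the result on the absolute scale used in the Sample size section.
- Limit the similarity sentence to the overall unadjusted estimate.

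In the Pre-specified subgroup analysis section:

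- Give absolute risks by arm and risk differences in each poison, time and severity subgroup beside the interaction or trend test.

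The cost is a few lines of code and a short change to the text; no further data or patients are needed. The Background describes the final data analysis as still under way, so the change fits within it. The headline relative effect may look slightly smaller than the odds ratio alone would suggest.
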